A thorough description of the intervention, and modifications of the intervention, following the TIDieR guidelines [33], is included in Additional file 3, and the full set of strength training descriptors, as suggested by Toigo and Boutellier [35], are presented in Table 1. An online instruction video of the exercises will be made available upon publication of the main results of the trial, and a link to these is provided in Additional file 3.

**Table 1 Tab1:** Strength training descriptors [35] of the exercises performed in the intervention group

	Phase 1	Phase 2	Phase 3
Load magnitude	15–20 RM	10–15 RM	8–10 RM
Number of repetitions	To volitional muscular fatigue	To volitional muscular fatigue	To volitional muscular fatigue
Number of sets	3 sets	4 sets (2 per exercise)	6 sets (2 per exercise)
Rest in-between sets	60 s	60 s	60 s
Sessions per week	7 per week	3.5 per week	3.5 per week
Duration of experimental period	5 weeks	5 weeks	6 weeks
Contraction modes per rep			
Concentric	2 s	2 s	2 s
Isometric	5 s	5 s	5 s
Eccentric	2 s	2 s	2 s
Rest between reps	2 s	2 s	2 s
Time under tension	9 s	9 s	9 s
Volitional muscular fatigue	Yes	Yes	Yes
Rest between sessions	24 h	48 h	48 h
Anatomical definition of exercise	Yes	Yes	Yes
Range of movement	Exercise 1: 80° ER	Exercise 1: 80° ER Exercise 2: 45° ABD	Exercise 1: 80° ER Exercise 2: 45° ABD Exercise 3: 45° ER

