#### Interventions – adherence

Lack of adherence to an exercise intervention is a major problem when aiming at investigating the effect of an intervention. In the previously described studies that include unsupervised resistance training in rehabilitation of SIS patients, monitoring adherence is either done using a log-book filled in by the patients [9, 12] or not described at all [13]. Using only patient-reported measures of adherence may limit the possibility of detecting which exercise dose is actually received by the patient. Accordingly, in a recent systematic review, the authors did not identify a single measure of patient-reported adherence to unsupervised home-based rehabilitation exercises to be sufficiently investigated [36]. Furthermore, findings from one previous study revealed that the dose of exercises reported in exercise diaries were 2.3 times higher than that collected through a system which monitored the exact TUT, being the total time a muscle resists weight during each set [37]. This clearly underlines the relevance of collecting objective data on exercise adherence. In addition, it seems unlikely that patients are always able to ‘take’ precisely the exercise dose prescribed. This issue was unfolded in a recent study, revealing that, just 2 weeks after initial instructions, only 7 out of 29 young healthy individuals were able to use the correct TUT, when performing shoulder exercises with an elastic band [38].

In the SExSI-Trial, adherence to the add-on progressive high volume resistance training intervention will be captured using the BandCizer^©^. The BandCizer^©^ is a small device which is mounted on the elastic band during exercises to measure the TUT, number of repetitions and total work load for all exercises performed. Exactly TUT is a promising objective measure of exercise adherence, for which the BandCizer^©^ is specifically developed and validated [39–41]. By directly monitoring the actual TUT for the prescribed exercises a more precise and objective distinction between adherent and less adherent patients will be possible.

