In both the intervention group and the control group, the time spent on exercises related to usual care will be monitored by self-report, using a text-message based system (SMS-track^©^). Each week all participants will receive a text-message question regarding the time spent on exercises performed for their shoulder disorder. Participants in the intervention group will be instructed not to include the time spent on the add-on intervention in this report.

In the intervention group, face-to-face adherence reminders will be given by the investigator administering the intervention at the initial intervention instruction and at each subsequent intervention appointment (week 0, 2, 5, 10 and 16). The reminders will focus on (1) the importance of performing all prescribed exercises and on correct execution of exercises; (2) emphasising that the intervention is an add-on to usual care, and should not be a substitution for this; and (3) counteracting important barriers to ongoing engagement with home exercises, as identified by Littlewood et al. [42], namely the simplicity of the intervention (lack of potential effectiveness), lack of an early appreciable symptom response, when symptoms are reduced to a certain point, and a lack of self-efficacy.

Intervention adherence will further be enhanced by supplying a leaflet with the programme to stick on the fridge, and via the proactive follow-up intervention appointments, aspects known to improve patients adherence to a home-based exercise programme [42]. For an English version of the leaflets, see Additional files 4, 5 and 6.

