#### Statistical methods – additional analyses

##### Subgroup analyses

For the outcomes SPADI score, abduction MVC and external rotation MVC, subgroup analyses investigating the modifying effect of scapula dysfunction, scapula dyskinesia, temporal summation of pain, conditioned pain modulation, pain pressure threshold (site 1) and pain catastrophizing, respectively, will be conducted. These will be performed using a cLMM, similar to the corresponding main analyses, but including a dichotomised value for the first measurement of the relevant variable as the interaction term and reporting the effect estimates for each subgroup.

The following sensitivity analyses will be performed for the primary outcome and reported together with the primary analyses in the primary trial report:A per protocol analysis, similar to the primary analysis, will be performed. From the IG, only patients who attended intervention appointments on weeks 0, 5 and 10 will be included in this analysis, while all patients in the CG will be included.Adjusted cLMM to adjust the effect of treatment allocation on SPADI score for any baseline differences between groups. Baseline variables will be included as covariates if (1) the difference between groups is more than 0.3 of the common SD for continuous outcomes, or (2) proportions are significantly different (*P* < 0.05) between groups, for binary outcomes.Sensitivity analyses to investigate the importance of the clinometric properties of the SPADI score may be relevant. This is based on a very recent study [58], which evaluates the SPADI score using the Rasch model. The study was published after initiation of this trial.

Three exploratory dose-response analyses will be performed. Only participants in the IG will be included in these analyses. First, the interacting effect of adherence to the intervention, TSP and CPM, on change in external rotation MVC, abduction MVC and SPADI score (outcomes), will be investigated. Secondly, whether the effect of TSP and CPM is mediated by adherence to the intervention will also be assessed. These analyses will be conducted as available-case analyses.

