#### Statistical methods  – analysis population and missing data

All main analyses will be conducted as intention-to-treat analyses, including all randomised participants, regardless of protocol adherence. Participants will be analysed as randomised. To create a full analysis dataset for the intention-to-treat analyses, missing outcome data will be imputed using multiple imputations based on the variables of all previous scores in the relevant outcome, age, sex and allocation.

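### The per-protocol analysis filters one arm only, on attendance after randomisation, so it is not a randomised comparison and may be biased, plausibly but not certainly towards the intervention

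*Protocol article*

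**What the plan says.** In the protocol article, the section on additional analyses introduces a short list with the statement "The following sensitivity analyses will be performed for the primary outcome and reported together with the primary analyses in the primary trial report". The first item is "A per protocol analysis, similar to the primary analysis, will be performed". Its population is fixed in both arms. For the intervention group the rule is "From the IG, only patients who attended intervention appointments on weeks 0, 5 and 10 will be included in this analysis". The control group, by contrast, is not filtered at all: "while all patients in the CG will be included". No attendance or adherence criterion is set for controls, and no adjustment for the selection is described.

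Three other places bear on this:

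- The section on analysis population and missing data states: "All main analyses will be conducted as intention-to-treat analyses, including all randomised participants, regardless of protocol adherence".
- The section on adherence describes a sensor on the elastic band that records time under tension (TUT), and says that with it "a more precise and objective distinction between adherent and less adherent patients will be possible". The per-protocol set does not use this measure.
- The same section lists barriers to continued home exercise. One is the absence of an early noticeable benefit. Another arises "when symptoms are reduced to a certain point".

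**The concern.** Attendance at weeks 5 and 10 is behaviour after randomisation. It can depend on motivation, pain and how the shoulder is recovering, all of which can also affect SPADI. Intervention patients who stop coming are removed. Control patients of the same type, who would have stopped coming had they been allocated the programme, stay in and contribute to the control mean. The difference between the two sets therefore mixes any treatment effect with a difference in prognosis, and it need not be zero when the treatment does nothing.

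The model adds a second problem. The analysis otherwise follows the primary one, a constrained linear mixed model. As usually understood, the constraint sets the two arms' baseline means equal. Randomisation justifies that for the full arms, but not once one arm has been filtered.

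What is at stake is how a sensitivity analysis printed beside the primary result is read. If it agrees with the primary analysis, it will look like confirmation. If it shows a larger effect, it will look like the effect of following the programme. It supports neither reading as defined.

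**Working it through.** **Inputs from the article (Sample size; Statistical methods).** SD of SPADI change 19.5; target difference 10 points; two-sided 5% level; 100 patients per group. These fit together: 2 × (1.960 + 1.645)² × 19.5² / 10² = 2 × 13.0 × 3.80 ≈ 99 per group, against the stated 100. The per-protocol rule itself carries no figure to reproduce.

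**Inputs not in the article, assumed here.** q is the share of the intervention group meeting the attendance rule. g is the difference in SPADI improvement between attenders and non-attenders that is unrelated to treatment. A positive g means attenders would do better anyway.

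**Bias with no treatment effect.** Let attenders improve by a on average and non-attenders by b, so g = a − b.

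- Intervention patients retained: mean a.
- All controls: mean q·a + (1 − q)·b.
- Difference: a − q·a − (1 − q)·b = (1 − q)·g.

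**Rejection rates.** These come from simulation with 10,000 null trials per setting: 100 controls, 100q intervention patients, total SD held at 19.5, two-sided t-test on change scores. IG is the intervention group and CG the control group.

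| Excluded (1 − q) | g | Bias, SPADI points | Significant, either way | Favouring IG | Favouring CG |
|---|---|---|---|---|---|
| 20% | 0 | 0 | 5.0% | 2.5% | 2.5% |
| 20% | +5 | +1.0 | 6.1% | 5.2% | 0.9% |
| 20% | +10 | +2.0 | 10.0% | 9.6% | 0.4% |
| 40% | +5 | +2.0 | 9.2% | 8.7% | 0.5% |
| 40% | +10 | +4.0 | 24% | 24.0% | <0.1% |
| 20% | −5 | −1.0 | 6.2% | 1.0% | 5.3% |
| 40% | −5 | −2.0 | 9.3% | 0.4% | 8.9% |

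Hand check of the +10 rows by normal approximation:

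- 20% excluded: SE = 19.5 × √(1/80 + 1/100) = 2.93. The shift is 2.0/2.93 = 0.68, and P(Z > 1.96 − 0.68) ≈ 10%.
- 40% excluded: SE = 19.5 × √(1/60 + 1/100) = 3.18. The shift is 4.0/3.18 = 1.26, and P(Z > 1.96 − 1.26) ≈ 24%.

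With 10% excluded and g = +5, the bias is 0.5 points and the rejection rate stays at about 5%. The problem is small if nearly everyone attends.

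**Check on the replacement.** A complier-average effect divides the intention-to-treat difference by q. If allocation has a mean effect e in those classed as non-compliers, then ITT = q × (complier effect) + (1 − q) × e, so ITT/q = complier effect + e × (1 − q)/q. For an assumed e of 5 points:

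- q = 0.8: 5 × 0.2/0.8 = 1.25 points too high.
- q = 0.6: 5 × 0.4/0.6 = 3.3 points too high.

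If the programme does nothing for anyone, both terms are zero and the estimate is unbiased. The compliance definition therefore matters for size, but not for validity under the null.

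**The case against.** **The primary analysis is safe.** Every main analysis is intention-to-treat with all randomised patients, the per-protocol set is labelled a sensitivity analysis, and its rule is stated openly. Nothing in the article lets it override the primary result. This stands. A reader might take the 10% or 24% as the trial's type I error. They are rejection rates of a secondary check under assumed inputs.

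**The direction is not known.** A reader might infer that the rule must favour the intervention. The article does not support that. Its barriers to exercise point both ways: patients may disengage because they feel no early benefit (bias towards the intervention) or because they already feel better (bias against it). Better prognosis among attenders is the more usual expectation, so bias towards the intervention is plausible, but no more than that.

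**The simulation is not the planned model.** It uses a change-score t-test with complete follow-up, not the constrained mixed model. The rejection rates are illustrative. The formula (1 − q)·g follows from the means alone.

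**The visits are not arbitrary.** Table 1 sets phases of 5, 5 and 6 weeks, so weeks 0, 5 and 10 are when the three phases begin. The rule picks patients instructed at the start of each phase. A reader might also infer that sensor adherence is ignored altogether, but it has its own planned dose-response analyses. Both points stand. They explain the rule but do not make the comparison randomised. Controls have no such appointments, so the same filter cannot be applied to them, and that is a reason to use a method that needs no filter.

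**A complier analysis has its own weak point.** Intervention patients are instructed straight after randomisation. Someone who misses only week 10 has been taught phases 1 and 2. Counting that person as untreated strains the exclusion restriction and inflates the estimate if partial attendance helps. This stands and shapes the fix.

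**Conclusion.** The point holds in a limited form. The per-protocol comparison selects on behaviour after randomisation in one arm only. It is therefore not a randomised comparison and can differ from zero with no treatment effect. Its bias is (share of intervention patients excluded) × (attenders' advantage unrelated to treatment). With 20% or 40% excluded and a 10-point advantage, both assumed, that is +2 or +4 points, or 20% to 40% of the 10-point difference the trial is sized for. With no advantage the bias is zero, and with a disadvantage it changes sign. The documents settle neither the size nor the sign.

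The primary conclusion does not depend on this. What needs correcting, before the analysis is run, is a supporting analysis that cannot carry the support a reader would draw from it.

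**What to change.** Replace the asymmetric set with a complier-average causal effect for 16-week SPADI change, using allocation as the instrument and keeping all randomised patients in both arms. Report it beside the intention-to-treat estimate.

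- **Compliance definition.** Use one under which non-compliers received little or no programme, that is, any meaningful exposure counts as compliance. Alternatively, use sensor-measured TUT as a continuous dose, set to zero in controls.
- **Three-visit definition.** Show attendance at weeks 0, 5 and 10 only as a variant, with a note that it overstates the effect if partial attendance helps.
- **Attendance-based set.** If it is still reported, label it non-randomised and do not cite it as support for the primary result.

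The cost is a change to the analysis text and one extra model on data already being collected. There are three downsides to state openly:

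- The interval is wider than for intention-to-treat.
- The exclusion restriction (allocation does nothing for those with no exposure, or acts only through the measured dose) cannot be tested.
- Controls are assumed not to receive the programme. The article supports this only in part. The programme is delivered to the intervention group, and the online exercise video "will be made available upon publication of the main results of the trial", but usual care may itself include exercises at the therapist's discretion.

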### Sample size

The sample size estimation is based on the primary outcome SPADI. Studies on patients with SIS have shown standard deviations (SD) for SPADI change score after 11–12 weeks of between 17 [12] and 18.5 [56], while longer durations seem to entail larger SDs, with a SD of 22 reported for SPADI change from 0 to 22 weeks [12]. The latter is similar to our own unpublished data from SIS patients, showing a SD of 22.5 for SPADI change from 0 to 6 months. Based on this previous data, we expect a common SD of 19.5 for SPADI change values from week 0 to 16, the primary outcome. For the purpose of this study, the MCID for SPADI will be considered to be 10 points, based on previous studies [45, 48]. The negative effect that any dropouts will have on the statistical power will, to some degree, be reduced by the use of multiple imputation. However, the imputation of data will not fully redeem this, as multiple imputation can cause an underestimation of the effect and a larger variation in outcomes. Therefore, we aim at having a high power of 95% to verify an effect equal to or higher than the MCID of 10 points on SPADI, at a 5% significance level. To obtain this, a total of 200 patients will be required (100 in each group). This corresponds to a power of 89.7% in case of a 20% dropout and a power of 85.4% in case of a 40% dropout.

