**Fig. 2 Fig2:**
[figure not shown]
Visualisation of changes in SPADI score in the intervention and control group, respectively (example, not based on data)

For comparison of binary outcomes, proportions will be compared using a χ^2^ test, and odds ratio estimates and corresponding 95% CIs will be reported.

Results from analyses comparing IG and CG for all primary and secondary outcomes will be reported in the second paper outlined in the ‘Dissemination policy’ section, except for the results on secondary outcomes regarding pain sensitisation and scapula dyskinesia, which will be reported in the third and fourth paper outlined in the ‘Dissemination policy’ section, respectively.

*P* values will be reported to the fourth decimal. For all tests, a two-sided significance level of ≤ 0.05 will be applied. All analyses will be conducted using up-to-date versions of SPSS and SAS.

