### Dissemination policy

All results from the study, be they positive, negative or inconclusive, will be published in international scientific journals. The project leader will enforce publication. Furthermore, the results will be presented at national and international conferences. Working titles for scientific publications are listed below. In the primary trial report, all collected outcomes will be defined and referenced to the dissemination plan below if data or analyses are not reported in the primary trial report.The Strengthening Exercises in Shoulder Impingement trial (The SExSI-Trial): Protocol for a pragmatic, assessor blinded, parallel-group, randomised, controlled, superiority trial investigating the effectiveness of adding a simple shoulder strengthening exercise programme to usual care, in patients with long-lasting subacromial impingement syndrome.The effectiveness of adding to usual care a simple programme of Strengthening Exercises In Subacromial Impingement patients (The SExSI-Trial): A randomised controlled trial (Primary trial report focusing on the primary outcome and analysis, as well as supportive secondary analyses for the primary outcome).The dose-response relationship between adherence to the intervention and changes in shoulder strength and patient-reported shoulder function: Pre-defined secondary analyses from the SExSI-Trial.The effectiveness of the SExSI-Trial add-on intervention on pain sensitisation, the modifying effect pain sensitisation on treatment outcomes and mediating effects of pain sensitisation on the dose-response relationship between intervention adherence and changes in outcomes: Pre-defined secondary analyses from the SExSI-Trial.The modifying effect of scapula dysfunction at baseline on shoulder strength and function outcomes and the effectiveness of the add-on intervention on scapula dysfunction: Pre-defined secondary analyses from the SExSI-Trial.

Additionally, the results of this study will be communicated directly to the participants, who will be encouraged to comment on disseminated trial results in order to improve their further public dissemination. Furthermore, trial results will be disseminated to the public in general through the daily press.

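### The adjusted SPADI sensitivity analysis picks its covariates by chance baseline imbalance rather than prognosis, so it adds almost nothing to the primary analysis

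*Protocol article*

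**What the plan says.** The section Statistical methods – additional analyses of the Protocol article lists sensitivity analyses of the primary outcome, to be reported with the primary analysis. One is an adjusted version of the constrained linear mixed model (cLMM) for SPADI. Its covariates are chosen by observed imbalance. For continuous variables: "Baseline variables will be included as covariates if (1) the difference between groups is more than 0.3 of the common SD for continuous outcomes". For binary variables the condition is that "proportions are significantly different (*P* < 0.05) between groups, for binary outcomes". Prognostic strength is not a criterion, and no candidate variables are named.

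Three other places bear on this:
- Statistical methods – outcomes: the primary cLMM already takes in baseline SPADI and the interim SPADI scores as repeated measurements.
- The section on analysis population and missing data: age, sex and earlier scores are used, but only to impute missing outcomes.
- Binary secondary outcomes: "For comparison of binary outcomes, proportions will be compared using a χ^2^ test", with an odds ratio and no covariates. Table 2 puts the two scapula tests here. The Dissemination policy shows that at least one of them has a baseline value, since a planned paper concerns "The modifying effect of scapula dysfunction at baseline on shoulder strength and function outcomes".

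**The concern.** The Allocation section describes a computer-generated sequence in permuted blocks of random sizes, concealed in sealed envelopes. If that is carried out as written, any baseline difference between the groups is chance. A rule triggered by the size of that difference then picks variables by luck. A variable unrelated to SPADI enters as easily as a strong predictor, and a strong predictor that happens to be balanced stays out.

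This affects how the result is read. Adjustment in a randomised trial is useful mainly because it removes outcome variation that baseline variables explain, and that depends on prognosis, not on imbalance. If no variable passes the thresholds, the adjusted and primary analyses are the same model, and their agreement says nothing about robustness. If some do pass, which ones is known only once the data are in.

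**Working it through.** **Inputs.** From the Sample size section: 100 per group, SD of SPADI change 19.5, "at a 5% significance level", the aim "we aim at having a high power of 95" per cent, and the target "to verify an effect equal to or higher than the MCID of 10 points on SPADI". From Statistical methods – outcomes: "For all tests, a two-sided significance level of" 0.05. From the additional analyses: thresholds of 0.3 SD and P < 0.05. The number of candidate covariates, their correlation and their prognostic strength are not given, so those values below are assumptions.

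**1. The plan's own figure.** n per group = 2 × (1.960 + 1.645)² × 19.5² / 10² = 98.8, so 99 per group and 198 in total. The stated 200 is reproduced. Power at 100 per group is 95.2% (normal) or 95.0% (noncentral t).

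**2. Chance that one covariate enters.** For a continuous variable the standard error of the standardised difference is √(2/100) = 0.1414. Then z = 0.3 / 0.1414 = 2.121, and the two-sided probability is 0.0339 (0.0351 with t). For a binary variable it is 0.05 by construction. The binary rule corresponds to 1.96 × 0.1414 = 0.277 SD, so the two rules are about equally strict. A given continuous predictor, however strong, is left out with probability 1 − 0.034 = 0.966.

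**3. Chance that no covariate enters.** With c continuous and b binary independent candidates this is (1 − 0.0339)^c × 0.95^b.

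| Assumed candidates (c + b) | P(none selected) |
|---|---|
| 3 + 1 | 86% |
| 5 + 2 | 76% |
| 6 + 2 | 73% |
| 10 + 4 | 58% |
| 10 + 5 | 55% |
| 15 + 5 | 46% |
| 14 + 6 | 45% |

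Correlation between candidates raises these values. For 6 + 2 they become 76% (correlation 0.3) and 80% (0.5); for 10 + 4 they become 64% and 71%.

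**4. What the rule gains.** Simulation: 20,000 trials per setting, 100 per group, five independent continuous candidates of which one is prognostic, linear model in place of the cLMM. The correlation of that covariate with the outcome and the true difference of 6 points are assumed; 6 points leaves room for power to differ.

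| Correlation with outcome | Quantity | No adjustment | Protocol rule | Prognostic covariate named in advance |
|---|---|---|---|---|
| 0.3 | Power | 58.3% | 58.3% | 62.1% |
| 0.5 | Power | 58.0% | 58.2% | 70.0% |
| 0.3 | Type I error | 5.0% | 4.8% | 5.1% |
| 0.5 | Type I error | 5.0% | 4.5% | 5.0% |

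The rule selected nothing in 83% to 84% of these trials, in line with (1 − 0.0339)^5 = 84%.

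**5. At the planned difference of 10 points.** If named covariates explain a further 5, 10, 20 or 30% of the variance (assumed), the SD becomes 19.5 × √(1 − R²). Power at 100 per group then moves from 95.2% to 96.1, 96.9, 98.2 or 99.1%. With 80 per group it moves from 90.0% to 91.4, 92.8, 95.2 or 97.2%.

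**6. Scapula tests.** Assume 100 per group, a conditional log odds ratio of −0.7, and a binary baseline result with log odds ratio 1 or 2 for the outcome. Logistic adjustment then moves power from about 65% to 67%, or from about 49% to 57%. The standard error of the log odds ratio does not shrink: it is about 0.29 unadjusted against 0.30 and 0.33 adjusted. The gain comes from the larger conditional estimate.

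**The case against.** The strongest reply is about scope. The rule governs one supportive analysis. The primary model already contains baseline SPADI, probably the best single predictor, and candidates such as pain last week and catastrophizing may overlap with it, so the further variance they explain is unknown. This stands, and it limits the size of the point.

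Second, the stated aim of the analysis is to adjust for baseline differences, so one may say that it has nothing to do when there are none. That is consistent with the text. But the check is then empty in most trials under the smaller assumed lists, and when it is not empty it acts on imbalance that may have no bearing on SPADI.

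Third, the selection frequencies rest on an assumed list. An article may leave the list to a fuller document, and the measurement schedule in Fig. 1 is not shown. This stands for the figures in step 3. It does not touch the 3.4% per continuous variable, nor the rule itself, which the article states outright.

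A reader might also infer more than the documents support:
- **That the analysis is not pre-specified.** The model, outcome and thresholds are fixed in advance and the analyst is blinded to allocation. Only the selected set depends on the data.
- **That the error rate is inflated.** In the simulation the rule was slightly conservative.
- **That the chi-squared tests are wrong.** They are valid under randomisation; adjustment offers some power, not a smaller standard error.
- **That both scapula tests have a baseline value.** This is explicit only for scapula dysfunction. For dyskinesia the article speaks of a first measurement without fixing its timing.

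**Conclusion.** The concern holds for the adjusted SPADI analysis. The rule selects on chance: about 3.4% per continuous variable and 5% per binary variable at 100 per group. For assumed lists of 4 to 20 independent candidates, the adjusted analysis coincides with the primary one in 45% to 86% of trials, and more often if the candidates are correlated. In the simulated settings it raised power by at most 0.2 percentage points, against about 4 to 12 points for a prognostic covariate named in advance.

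It would be wrong to conclude that the primary result is biased or that the trial is underpowered because of this. The primary estimate, its error rate and the sample size are untouched. What is lost is the information that a supportive analysis in the primary trial report could have given, and a covariate set that is known beforehand. The change is worth making because it is nearly free. The binary outcomes are a minor, optional matter.

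**What to change.** In Statistical methods – additional analyses, delete the 0.3 SD and P < 0.05 conditions. Before unblinding, name a few baseline covariates chosen for their expected link to SPADI, and fit them in the adjusted cLMM whatever the observed balance. Age, sex, pain last week and pain catastrophizing score are examples already collected. This also removes an awkward case that the present rule leaves open: if baseline SPADI itself differed by more than 0.3 SD, it would be added as a covariate to a model that already holds it as a response.

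Do not list corticosteroid injection before randomisation unless its recording is confirmed. The concomitant care section says that injections are recorded, but not their timing relative to randomisation.

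Optionally, analyse the scapula dysfunction test by logistic regression adjusted for its baseline result, and the dyskinesia test likewise if it was measured before randomisation.

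Cost: analysis wording only, with no new data, visits or patients. The downsides are a few degrees of freedom and, for the optional part, an odds ratio that is conditional rather than marginal and should be labelled so.
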